## Molecular analysis

Molecular analysis of parasite DNA will be performed in batches and results will not be available for clinical application. Wild-type chloroquine susceptible parasites are distinguished from mutant chloroquine resistant parasites by nested-PCR followed by allele specific restriction digest, following standard procedures available on our Website: <http://www.medschool.umaryland.edu/cvd/[name].asp>.

Cases of parasitemia from day 14 through day 28 will undergo MSP-2 genotyping following the protocol published by Cattamanchi , et al (58) or an updated method if available at the time of analysis. Recrudescent infection will be defined as a PCR product from the failure day that is within 10 base pairs (bp) of a PCR product present on the initial day of infection. A new infection will be defined as a PCR product that is more than 10 bp different in size from the strain(s) present during the initial infection. Others will be labeled as indeterminate and may be investigated further.

## Specimen Shipment

Specimens will be shipped to the University of Maryland for confirmatory tests of data generated in Malawi and for other analysis requiring equipment that is not available in Malawi. Dried filter paper specimens that are not known to carry infectious agents can be transported without any special precautions. If cryopreserved parasites and sera need to be shipped to collaborating laboratories, they will be transported in liquid nitrogen dry shippers that meet all the relevant requirements and specifications.

# Assessment of Safety

## Specification of Safety Parameters

Complete blood count, ALT and creatinine will be measured every time an episode of clinical malaria occurs, at day 14 after the treatment and at approximately 3-month intervals (see study schedule). An age-appropriate neurological examination will be conducted after resolution of the initial illness, at two regular intervals, and at the last visit of the study.

## Methods and Timing for Assessing, Recording, and Analyzing Safety Parameters

### Adverse Events definition

ICH E6 Good Clinical Practice Guidelines defines an Adverse Event (AE) as any untoward medical occurrence in a patient or clinical investigation subject administered a pharmaceutical product regardless of its causal relationship to the study treatment. An AE can therefore be any unfavorable and unintended sign (including an abnormal laboratory finding), symptom, or disease temporally associated with the use of medicinal (investigational) product. The occurrence of an AE may come to the attention of study personnel during study visits and interviews or by a study recipient presenting for medical care. Any medical condition that is present at the time of the participant is enrolled will be considered a baseline condition, and not reported as an AE. However, if the severity increases, it will be recorded as an AE.

**Severity** All adverse events will be assessed by the investigator using a protocol defined grading system in Appendix III and the DMID Pediatric Toxicity Tables. For events not included in the protocol defined grading system, the following guidelines will be used to quantify severity.

- **Mild** - causes minimal discomfort and does not interfere with normal activities.
- **Moderate** - sufficiently discomforting to interfere with normal activities.
- **Severe** - incapacitating, prevents normal activities.
- **Life**-**Threatening –** immediately life threatening however death did not occur.

Changes in the severity of an AE should be documented with the maximum severity. Adverse events characterized as intermittent require documentation of onset and duration of each episode.

**Relationship to study products**: The investigator’s assessment of an AE's relationship to study drug is part of the documentation process, but it is not a factor in determining what is or is not reported in the study. If there is any doubt as to whether a clinical observation is an AE, the event should be reported. All AEs must have the relationship to study product assessed using the following terms: associated or not associated. In a clinical trial, the study product must always be suspect. To help assess relationship, the following guidelines are used.

- Associated – There is a known temporal relationship *and/or*, if re-challenge is done, the event abates with de-challenge and reappears with re-challenge *and/or* the event is known to occur in association study product or with a product in a similar class of study products
- Not Associated - The AE is completely independent of study product administration; and/or evidence exists that the event is definitely related to another etiology.

### Serious Adverse Events

**Serious Adverse Event (SAE)**: An SAE is defined as an AE meeting one of the following conditions:

- Death during the period of protocol defined surveillance
- Life Threatening Event (defined as a subject at immediate risk of death at the time of the event)
- An event requiring inpatient hospitalization or prolongation of existing hospitalization during the period of protocol defined surveillance
- Results in a persistent or significant disability/incapacity.
- Any other important medical event that may not result in death, be life threatening, or require hospitalization, may be considered a serious adverse experience when, based upon appropriate medical judgment, the event may jeopardize the subject and may require medical or surgical intervention to prevent one of the outcomes listed above. Examples of such medical events include allergic bronchospasm requiring intensive treatment in an emergency room or at home, blood dyscrasias or convulsions that do not result in inpatient hospitalization, or the development of drug dependency or drug abuse.

All SAEs will be:

- recorded on the AE/SAE CRF
- followed by a study clinician until either resolution or stabilization
- reviewed and evaluated by the study coordinator or investigator.

### Procedures to be Followed in the Event of Abnormal Laboratory Test Values or Abnormal Clinical Findings

Described above

## Reporting Procedures

The Investigator is responsible for reporting all AEs that are observed or reported during the study, regardless of their relationship to study product.

### Reporting AEs

AEs including local and systemic reactions not meeting the criteria for “serious adverse events” should be captured on the appropriate case report form. Information to be collected includes event description, time of onset, investigator assessment of severity, relationship to study product, time of resolution of the event, seriousness, and outcome. All adverse events occurring while on study must be documented appropriately regardless of relationship. All AEs will be followed to adequate resolution or stabilization.

Any medical condition that is present at the time that the subject is screened and found eligible should be recorded and be considered as baseline and not reported as an AE. The child should receive appropriate treatment and follow-up for these events. Non-eligible children will be referred for treatment at the Ndirande District Health Centre or transport to the hospital will be arranged. If a baseline condition deteriorates at any time during the study, it should be recorded as an AE.

### Regulatory Reporting for Studies Conducted Under DMID‑Sponsored IND for SAEs

SAEs will be reported as described in the table below

|  | **DMID via PPD**  **(sponsor)** | **FDA** | **COMREC** | **University of Maryland** | **Pfizer**  For participants who received azithromycin in the past 28 days |
| --- | --- | --- | --- | --- | --- |
| **Contact information** | Medical Affairs/Pharmacovigilance  PPD Inc.  SAE Fax line [name] or via the internet  [contact] | DMID to contact | Hand delivery or email ([contact]) | Via BRAAN system | [name], PCO Safety Head, Africa  [[contact]](mailto:[contact])  or  [contact] |
| **Death or a life threatening event** | 24 hours | 7 days | Within 24 hours | Within 48 hours | Immediately |
| **SAE (not included above) that is related and unexpected** | Within 72 hours | Within 15 days | Within 24 hours | Within 48 hours | Within 24 hours |
| **Study drug (not included above) related SAEs** | Within 72hours | Reported annually | Within 72 hours | Annual summary | Within 24 hours |
| **Other SAEs** | Within 72hours | Annual summary | Within 72 hours | Annual summary | Within 24 hours |
| **AEs (not SAEs)** | Annual summary* | Annual summary* | Annual summary* | Annual summary* | End of study report |

.* Unless otherwise requested by the ISM, the sponsor, the FDA or the investigators.

Other supporting documentation of the event may be requested by the pharmacovigilance contractor and should be provided as soon as possible.

All SAEs will be followed until satisfactory resolution or until the Principal Investigator or co-investigator deems the event to be chronic or the subject to be stable.

## Type and Duration of Follow-up of Subjects after Adverse Events

Participants will be followed for a total of one year, so many AEs will resolve during active enrollment in the study. AEs that remain unresolved at the end of the participants enrollment in the study will be followed until their resolution or until they have stabilized.

## Halting Rules

The data safety monitoring board (DSMB, described below) will meet after the initial follow up period for the first 150 participants and then at least every year thereafter. The data to be reviewed at the interim analysis meeting will include safety and efficacy results. Safety data will be presented as line lists of SAEs with descriptions and relatedness to study drug, as well as tallies of grade 3 and 4 AEs by treatment arm. An excess of SAEs in one arm may lead the DSMB to recommend suspending one or more arms of the study, to request further data or to require another safety analysis at a specified interval. Efficacy data will be presented including results through day 28 for all subjects in the review group. Less than or equal to 75% adequate clinical response at day 28 will lead to a discussion in the DSMB about suspension of that arm of the trial. This number alone, however, will not require stopping the study. The efficacy of all study arms is likely to be very high. This plan is subject to review by the malaria DSMB and the schedule may be changed according to their recommendation.

All SAEs will be reviewed by the independent safety monitor (ISM). The ISM may request an *ad hoc* meeting of the DSMB after the occurrence of any SAE that is associated with the study drug. Reviews by the IRB, the sponsor or the FDA may also result in suspension of further enrollment or participation.

## Safety Oversight (ISM plus DSMB)

Safety oversight will be under the direction of the Malaria DSMB established by DMID. The ISM, a local pediatrician who is not associated with the study, will review all SAEs and make periodic checks of grade 3 and 4 AEs. The ISM may request an ad hoc DSMB meeting at any time, and is encouraged to do so if an SAE occurs that the ISM deems associated with the study drug. The DSMB will operate under the rules of a DMID-approved charter that will be written and approved at the organizational meeting of the DSMB. The DSMB will meet after the first 150 participants reach the 28th day after the first episode of malaria. They will then meet at least annually. At this time, each element that the DSBM needs to assess will be clearly defined. The DSMB will advise DMID of its findings.

# Clinical Monitoring

## Site Monitoring Plan

Site Monitoring will be conducted to ensure that human subject protection, study procedures, laboratory procedures, study intervention administration, and data collection processes are of high quality and meet sponsor, GCP/ICH, and regulatory guidelines, and that the study is conducted in accordance with the protocol and sponsor SOPs. DMID, the sponsoring agency, or its designee will conduct site monitoring visits as detailed in the monitoring plan or in the Manual of Procedures.

Site visits will be made at standard intervals as defined by DMID and may be made more frequently, as directed by DMID. Monitoring visits will include, but are not limited to, review of regulatory files, accountability records, case report forms, informed consent forms, medical and laboratory reports, and protocol compliance. Study monitors will meet with the study coordinator and/or investigators to discuss any problems and actions to be taken and document visit findings and discussions.

# Statistical Considerations

## Study Hypotheses

The study is powered to compare each combination individually with chloroquine monotherapy. The power is restricted to pairwise comparisons. The goal is to identify superiority of the combination arm in comparison with the monotherapy arm.

Primary objective:

Null hypothesis: Chloroquine monotherapy for treatment of malaria leads to the same annual incidence of malaria episodes as treatment with chloroquine combined with one of the partner study drugs.

Alternative hypothesis: The annual incidence rates of malaria episodes will differ between the group treated with chloroquine monotherapy and the group treated with chloroquine combined with a partner study drug.

## Sample Size Considerations

In a previous longitudinal study of malaria in this population, we found that the mean annual incidence of malaria was approximately 2.5 episodes per year (59) with a standard deviation of approximately 2. Chloroquine is presently highly effective in treating malaria and has a prolonged prophylactic effect, so we have estimated a mean rate of 1.5 malaria episodes per year with chloroquine alone. We derived the sample size required to detect a decrease in the mean to 1.0 episodes per year assuming a Poisson distribution and using a 2 sided test with alpha= .05/3=.0166. The test size was adjusted to accommodate the 3 treatment versus control comparisons. With the above requirements and for a 2 treatment contrast, 120 subjects with complete observation are required per treatment arm to have 90% power (PASS 2005). To account for migration and other causes of attrition, we will enroll an additional 33% (40 subjects) in each regimen. We will accrue 160 per arm for a total of 640 subjects.

Because of the currently estimated efficacy of chloroquine alone in Malawi (in excess of 95%), we are unlikely to determine differences in initial administration (day 28) efficacy between the treatment arms. Power is limited as all arms should have very few early failures. Rates of anemia (<8 mg/dl) at the end of one year should be available in ~120 subjects per arm. The 95% CI half-width for the difference in anemia rates, calculating the variance with a rate of .2, is approximately .10. Thus, the selected sample size should be informative about larger treatment arm differences in anemia rates.

To determine the population pharmacokinetic curve for chloroquine, we have designed a randomized unbalanced study. All participants will have chloroquine levels determined prior to drug administration, at day 14 and at one additional randomly assigned time point. The assignment will be weighted to increase measurement on day two. Planned Interim Analyses

The DSMB will decide when it would like to conduct the interim analysis. The data to be reviewed at this meeting will include safety and efficacy data.

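### The protocol's only stated multiplicity adjustment is an equal Bonferroni split of .05/3; Holm's step-down would give more power at the same 5% family error and the same sample size

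*Protocol*

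**What the plan says.** Section 11.1 (Study Hypotheses) sets up three superiority contrasts: "The study is powered to compare each combination individually with chloroquine monotherapy". It limits the power claim to pairwise comparisons.

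Section 11.2 (Sample Size Considerations) gives the planning inputs:
- Control arm: "we have estimated a mean rate of 1.5 malaria episodes per year with chloroquine alone".
- Alternative: to "detect a decrease in the mean to 1.0 episodes per year assuming a Poisson distribution".
- Test: "using a 2 sided test with alpha= .05/3=.0166", with the reason "The test size was adjusted to accommodate the 3 treatment versus control comparisons".
- Result: 120 fully observed children per arm for 90% power on one two-arm contrast.
- Attrition: "we will enroll an additional 33% (40 subjects) in each regimen", and then "We will accrue 160 per arm for a total of 640 subjects".

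Section 11.3 (Final Analysis Plan) compares incidence rates between arms and reports Poisson rates with 95% confidence intervals. It names no multiplicity procedure and no decision level for the three primary contrasts. A statistical analysis plan may settle this, but none was available for this review.

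**The concern.** The only rule a reader can take from the protocol is that the 5% is divided equally, .05/3 to each contrast. Applied in one step, that rule holds every contrast to .0167 however strong the other two results are. Holm relaxes the hurdle as contrasts are rejected. The smallest p-value is tested at .05/3, the next at .05/2 and the last at .05, stopping at the first failure. It controls the family error under any dependence between the tests, including the dependence from a shared chloroquine arm.

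What is at stake is the second and third findings. The Rationale section expects all the combinations to be highly efficacious and chose partners that stay active for different lengths of time. Which contrasts succeed is therefore informative, and not only whether one does.

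**Working it through.** **Inputs (Section 11.2).** Control rate 1.5 and alternative 1.0 episodes per child-year, Poisson counts, 120 evaluable per arm, equal allocation, two-sided level .05/3 = .016667 (printed truncated as .0166; the difference is immaterial). Normal quantiles: 2.394 for two-sided .05/3, and 1.2816 for 90% power.

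**1. The protocol's own figure.** Poisson-regression sample size (Signorini) with a 50:50 binary covariate, baseline rate 1.5 and b = ln(1.0/1.5) = −0.4055:

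N = [z(α/2)·√V0 + z(power)·√V1]² / (1.5·b²), with V0 = 1/(0.5·0.5) = 4 and V1 = 1/0.5 + 1/(0.5·2/3) = 5.

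N = [2.394·2 + 1.2816·2.236]² / (1.5·0.1644) = 7.654² / 0.2466 ≈ 237.5 in total, or 118.8 per arm. That rounds to 119 per arm, and power at 120 is 90.3%. The stated 120 reproduces. Attrition: 120 + 40 = 160 per arm, and 4 × 160 = 640.

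**2. A plain Wald test of the rate difference.** n = (2.394 + 1.2816)²·(1.5 + 1.0)/0.5² = 13.51·10 = 135.1, so 136 per arm. At 120 per arm the standardised difference is 0.5/√(2.5/120) = 3.464. Power by level is:

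| Two-sided level | Power at 120 per arm |
|---|---|
| .05/3 (Holm step 1) | 85.8% |
| .05/2 (Holm step 2) | 88.9% |
| .05 (Holm step 3) | 93.4% |

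The gap between 90% in step 1 and 86% here comes from the variance formula, not from multiplicity. The table also shows where Holm's gain comes from. A contrast keeps its 86% guarantee and moves towards 93% once the others have been rejected.

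**3. Simulation of the four-arm trial.** 400,000 trials, Poisson totals, 120 child-years per arm, shared control arm, pairwise conditional z-tests.

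| Combinations truly at 1.0 | Power per effective contrast, Bonferroni → Holm | All effective ones shown | At least one rejection | Family error, Bonferroni → Holm |
|---|---|---|---|---|
| Three | 86.1% → 91.4% | 71.3% → 84.4% | 97.2% → 97.2% | not applicable |
| Two | 86.1% → 88.4% | 77.4% → 82.0% | 95.1% → 95.1% | 1.6% → 4.0% |
| One | 86.1% → 86.2% | same as per contrast | 87.1% → 87.1% | 3.1% → 4.3% |
| None | not applicable | not applicable | 4.5% → 4.5% | 4.5% → 4.5% |

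Family error stays below 5% throughout.

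**4. Sensitivity, all three effective.**
- At 136 per arm, where this test has about 90% power: per contrast 90.5% → 94.6%; all three 79.3% → 89.7%.
- Section 11.2 cites a standard deviation of about 2 at a mean of 2.5 in earlier data, so variance/mean = 4/2.5 = 1.6. With variance 1.6 times Poisson in every arm and 120 per arm: per contrast 63.8% → 71.6%; all three 39.3% → 56.9%.
- With the same spread expressed as a gamma variance of (4 − 2.5)/2.5² = 0.24: per contrast roughly 75% → 82%; all three 53% → 70%.

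The absolute power depends on these assumptions. The direction of the gain does not.

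**5. Sample size under Holm.** The first step is still .05/3, so the 119 to 120 per arm from step 1 is unchanged.

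**The case against.** **The protocol does not say the tests will be single-step.** The .05/3 appears only in the sample-size derivation. A reader might infer that each contrast will be judged at .0166 whatever the others show, but no section states this and none rules out a step-down. A statistical analysis plan could adopt Holm without touching any design figure. This stands, so the point concerns the only adjustment stated and not a confirmed decision rule.

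**Bonferroni is valid.** Its family error here is about 4.5%, which is mild conservatism. A reader might infer an error in type I control or a wrong sample size. Neither is supported: 120 per arm reproduces, and .05/3 is also the right sizing level under Holm.

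**Showing all three is not a stated target.** Section 11.1 restricts power to pairwise comparisons, and the largest gains need all three combinations to cut incidence by a third. The partners were chosen to differ, so equal effects are not assured. This also stands, and it is why the two-effective and one-effective rows matter.

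**Holm is not entirely free.** Simultaneous intervals that match it are less simple. Single-step intervals shown alongside can include no effect for a contrast that Holm rejects. The chance of rejecting a true null rises too, for example from 1.6% to 4.0% when two combinations work, though it stays within 5%.

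None of this removes the remaining point: Holm rejects everything the equal split rejects and sometimes more, at the same family error.

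**Conclusion.** The point holds as an optional improvement in efficiency. The equal .05/3 split is the only multiplicity adjustment the protocol states. It is valid, but Holm dominates it. The gain at 120 child-years per arm (1.5 against 1.0, Poisson, shared control) is about 5 points per contrast and 13 points for showing all three if all work. It is about 2 points per contrast if two work and about 0.1 point if one works. Holm adds nothing to the chance of at least one success and saves no children. The sizes rest on equal effects among the effective combinations and on the simple pairwise test used. Holm's dominance and its 5% family error rest on neither.

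**What to change.** Add one sentence to Section 11.3: the three primary contrasts against chloroquine are tested by Holm's procedure at family-wise two-sided .05. Leave .05/3 in Section 11.2 and describe it as the sizing level, which is Holm's first step. The 120 evaluable and 160 enrolled per arm stay as they are.

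State how intervals will be shown. If single-step simultaneous intervals are reported for simplicity, note that one of them may include no effect for a contrast that Holm rejects.

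The trial is open label, so the rule should be fixed before outcomes are compared by arm. Otherwise the cost is one sentence and the less tidy link between tests and intervals.

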| Late clinical or parasitologic failure (% per-protocol) | 0 (0) | 50 (57) |
| Outcomes unknown | 25 | 18 |
| Total | 105 | 105 |

Table 1: Outcomes of 28-day efficacy study of chloroquine vs. SP for the treatment of uncomplicated malaria among children in Blantyre, Malawi.

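### The 90% power in section 11.2 assumes pure Poisson counts, although the same paragraph cites an SD showing about 1.6 times Poisson variance; if that carries over, power at 120 completers per arm is about 63–74%

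*Protocol*

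**What the plan says.** Section 11.2 of the protocol (Sample Size Considerations) starts from an earlier longitudinal study in this population, with "approximately 2.5 episodes per year (59) with a standard deviation of approximately 2". Because chloroquine is now effective and has a long prophylactic effect, the control rate is lowered: "we have estimated a mean rate of 1.5 malaria episodes per year with chloroquine alone". The target is to "detect a decrease in the mean to 1.0 episodes per year assuming a Poisson distribution". The test is specified as "using a 2 sided test with alpha= .05/3=.0166", and the reason is given: "The test size was adjusted to accommodate the 3 treatment versus control comparisons". The result is that "120 subjects with complete observation are required per treatment arm to have 90% power (PASS 2005". Forty further children per arm are added for attrition, making 160 per arm and 640 in all. The PASS procedure and the formula are not named.

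The final analysis plan (section 11.3) bases the primary rates and intervals on the Poisson distribution. It counts the follow-up time of every child while enrolled, including children who later leave.

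**The concern.** A Poisson count with mean 2.5 has variance 2.5 and SD 1.58. The SD of about 2 quoted for this population means variance 4, or 1.6 times as much. This is the only figure for the variability of the primary outcome in the protocol, and it contradicts the distribution assumed three sentences later. No reason is given for expecting the excess variation between children to disappear at the new rates.

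Section 11.1 says that the study is powered for each combination against chloroquine alone. If power is really nearer two thirds or three quarters, the chance of missing the target effect is about 26–37% rather than 10%. A non-significant comparison could then be over-read as evidence that a partner drug does not reduce malaria incidence.

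**Working it through.** **Inputs (all section 11.2).** Rates 1.5 and 1.0 per child-year; two-sided alpha 0.05/3, so z = 2.394; power 90%, so z = 1.282; 120 completers per arm; earlier mean 2.5, SD 2.

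**1. Reproducing the stated figure.** The two-group Poisson-regression formula with baseline rate 1.5 is N = (z_a·√V0 + z_b·√V1)² / (1.5·[ln(2/3)]²), with V0 = 4 and V1 = 2 + 2/(2/3) = 5.
- N = (2.394×2 + 1.282×2.236)² / (1.5×0.1644) = 237.5, or 118.8 per arm, rounded up to 119.
- Power at 120 per arm: Φ[(√(240×1.5)×0.4055 − 2.394×2)/2.236] = Φ(1.299) = 90.3%.

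So the 120 and 90% follow from the stated two-sided inputs. That PASS used this formula is an inference. The formula fixes the null variance at a rate of 1.5 in both arms, which is too small when one arm is at 1.0.

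**2. Other Poisson calculations, same inputs.**

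| Method | Power at 120 per arm | n per arm for 90% |
|---|---|---|
| Rate difference, unpooled | 85.8% | 135.1 |
| Log rate ratio, Wald | 85.2% | 137.0 |
| Square-root transform | 86.2% | 133.7 |
| Conditional binomial (normal approximation) | 86.3% | 133.2 |
| Exact summation over Poisson totals, score test | 86.1% | about 135 |

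First row: (2.394 + 1.282)² × (1.5 + 1.0)/0.5² = 13.51 × 10 = 135.1, and power Φ[0.5/√(2.5/120) − 2.394] = 85.8%.

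**3. Allowing for the cited SD.** Two usual ways of carrying the excess to 1.5 and 1.0, both assumptions:
- *Negative binomial.* k = (4 − 2.5)/2.5² = 0.24. Summed variance 2.5 + 0.24×(1.5² + 1.0²) = 3.28. Power Φ[0.5/√(3.28/120) − 2.394] = 73.6%; n for 90% = 13.51×3.28/0.25 = 177.
- *Constant variance/mean 1.6.* Summed variance 1.6×2.5 = 4.0. Power Φ[0.5/√(4/120) − 2.394] = 63.5% (62.8% on the log scale); n for 90% = 216.

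The favourable formula of step 1, with information divided by 1.6, gives Φ[(√(240×1.5/1.6)×0.4055 − 4.788)/2.236] = 72%.

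**4. Counting partial follow-up.** Replace 120 by child-years per arm. The 140 row assumes that the 40 extra children average half a year. It is approximate for the negative binomial, where unequal follow-up does not reduce exactly to child-years.

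| Child-years per arm | Poisson | k = 0.24 | Variance/mean 1.6 |
|---|---|---|---|
| 120 | 86% | 74% | 63% |
| 140 | 91% | 81% | 71% |
| 160 (no attrition) | 95% | 86% | 78% |

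**5. Rate detectable with 90% power at 120 per arm.** Solve (1.5 − r)/√(variance/120) = 3.676. Poisson: r about 0.97. With k = 0.24, r = 0.90 gives 0.60/√(3.134/120) = 3.71, so r is about 0.90. With ratio 1.6, r = 0.85 gives 0.65/√(3.76/120) = 3.67, so r is about 0.85.

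**The case against.** The strongest reply is that the stated inputs do yield the stated figure. Step 1 bears this out, and the protocol is not obliged to use the two-rate formula. A reader might infer that 120 is an arithmetic slip, or that a one-sided test was run, since one-sided 0.05/3 needs about 116 per arm. Neither is supported: the text says two-sided, and a two-sided route reaches 119.

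The roughly four-point Poisson gap may also vanish in practice. About 135 child-years are needed, so the 40 extra children need contribute only about 15/40 = 0.4 year each.

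It is also fair to say that the SD does not fix a power figure. It is approximate, it comes from a trial of other drugs at a higher mean, and the protocol states no model for carrying it over. An earlier SD of 1.8 (assumption: k = (3.24 − 2.5)/6.25 = 0.118, ratio 3.24/2.5 = 1.296) would give 74–80% at 120 per arm. Using SD 2 literally in both arms would give 32%, but that sets a variance of 4 at means of 1.5 and 1.0, and the text does not ask for it. What stands is that the protocol quotes excess variance and then assumes none; both usual carry-over models fall short of 90% even with no attrition.

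Table 1 of the Background section ("Outcomes unknown | 25 | 18") might tempt a reader to conclude that the attrition allowance is too small. It counts unclassified 28-day outcomes, which are not lost child-time in a rate analysis, and this trial uses tracers. A reader might also infer that the final test will be anti-conservative; how it handles overdispersion may be settled in a statistical analysis plan that is not at hand.

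**Conclusion.** The point holds as an inconsistency between an input and an assumption in section 11.2, not as a calculation error. Under pure Poisson, power at 120 complete child-years per arm is about 86% rather than 90%, and partial follow-up may make up the difference. If the dispersion implied by mean 2.5 and SD 2 carries over to 1.5 and 1.0, power is about 63–74% at 120 per arm and about 78–86% at 160 full child-years. The ranges depend on that assumption and on the rounded SD. The documents do not support a single replacement figure, nor the claim that the trial must be enlarged.

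**What to change.** Keep 160 per arm and revise section 11.2:
- Name the formula or PASS procedure behind the 120.
- Replace the pure Poisson assumption with an overdispersed one, for example negative binomial, and say how the dispersion was derived from the earlier mean and SD.
- Restate power at 120 complete child-years per arm as about 86% under Poisson and about 63–74% allowing for the reported SD, with the carry-over labelled as an assumption.
- Give the combination-arm rate detectable with 90% power at 120 per arm: about 0.85–0.90 episodes per year against 1.5.

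This needs no further children and changes no procedure. The cost is a less favourable stated power.
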